##### Baseline (pre-intervention)

Questionnaire including background (demographics, current gait analysis practice, access to IGA equipment, barriers to gait analysis practice), attitudes (reasons for joining the study, anticipated changes in practice after the intervention, beliefs), confidence (self-rated), and knowledge (self-rated and multiple-choice question test)Objective structured clinical examination (OSCE) of a patient case: Assessment will be delivered on-line, recorded and scored against a standardised scoring sheet including gait-related clinical reasoning and treatment planning based on evidence and findings, problem-solving, systematicity of approach, ability to link various types of gait-related information, confidence in engagement with gait data, analysis of gait graphs, communication (including use of gait-related terminology, providing lay explanations to a parent), and implementation of biopsychosocial model or ICF to decision-making

##### Post intervention (immediately after 6-week intervention)

Questionnaire including attitudes (planning practice change, implemented practice change, beliefs), confidence (self-rated), knowledge (self-rated and multiple-choice question test), and satisfaction (experimental group only)OSCE of a different patient case (scored against the same criteria as at baseline)

##### Re-test (4-month post-intervention)

Questionnaire attitudes (planning practice change, implemented practice change, beliefs), confidence (self-rated), and knowledge (self-rated and multiple-choice question test)OSCE of a different patient case (scored against the same criteria as at baseline)

Knowledge and skills retention as well as attitudes will be measured between timepoints, with a focus on changes between baseline and immediately post intervention and at 4-month follow-up. Satisfaction questionnaire will contain 28 items, each assessed on a 5-point Likert scale, related to the relevance and scientific quality of the content, the educational structure, and delivery. Satisfaction feedback will be collected immediately after intervention delivery (experimental group).

### Sample size

Considering the study objectives and recommendations, the target sample size will be of a minimum 12 participants per trial arm; therefore, a minimum of 24 in total is anticipated. Guidance from the National Institute for Health Research (NIHR) indicates that a sample size of 30 is appropriate to answer the questions posed by a feasibility trial [23]. A lower number of participants will be better suited for an educational intervention for clinicians — it will ensure delivery of a high-quality learning experience and allow for active engagement with tutors during problem-based learning within the experimental group. Furthermore, the stakeholder focus groups including of clinicians and educators reviewed the proposed sample size and reported it as appropriate for the feasibility trial.

### Recruitment

Participants will be recruited via the largest national paediatric physiotherapy network (Association of Chartered Paediatric Physiotherapists) using bulletins, social media, and targeted emails to team leads across the UK. The advertisement will provide general information about the intervention and the research study together with inclusion and exclusion criteria. Upon expression of interest, participants will be screened against eligibility criteria, and the participant’s information sheet and consent form will be sent to prospective participants via email. Participants will return signed consent forms electronically to the research lead. In line with advice from the Clinician and Educator Focus Group (PPI-B), the recruitment of study participants will commence early to ensure that participants are able to make suitable arrangements in the workplace, such as request study leave and ‘block time’ to attend synchronous sessions etc.

#### Participant timeline

Time schedule of enrolment, intervention, and assessments is presented in Table 1. After the eligibility criteria screen and receipt of their written informed consent, 24 participants will be enrolled to the study. After random allocation to the trial arms, participants will receive access to the password-protected online platform hosted by Queen Mary University of London. All participants will be asked to complete the baseline assessment including the questionnaire (background, attitudes, knowledge, and skills) and objective structured clinical examination (OSCE) of a patient case (assessment will be delivered on-line, recorded, and scored against standardised scoring sheet). After completing the baseline assessment, participants assigned to the experimental arm will gain access to the pre-course learning resources (6 weeks prior to start of the course). The experimental group will commence the 6 week blocks of intervention including pre-recorded resources, problem-based learning tasks, discussion forums, and live sessions. At 6 weeks, participants from both arms will be asked to complete the second assessment including the questionnaire (attitudes, knowledge and skills, and satisfaction scores in experimental group only) and the second OSCE of a patient case. Four months after the intervention, participants in both trial arms will be asked to complete the third assessment including the questionnaire (attitudes, knowledge, and skills) and the OSCE of a patient case. Once all the data is collected, participants in the control group will gain access to the prereading resources and start the 6-weekly intervention sessions.

### Assignment of intervention

#### Allocation, concealment mechanism, and implementation

Participants who meet the inclusion criteria and return the consent form will be assigned an ID number in the Microsoft Excel spreadsheet. Participants will be assigned to groups randomly. In case there are more eligible physiotherapists than spaces, participants will be chosen by the number generation software which will be used in the allocation process. This will be conducted by an external person not related to the study or the research team. To avoid contamination, participants from the same healthcare trusts will be randomised to the same group.

Information about group randomisation will be provided in the participant’s information sheet. Participants in this study will not be blinded to the group allocation or deceived. This was discussed in the stakeholder focus groups who agreed that in the context of clinical practice, deceiving participants could mean a loss of their study/annual leave if pre-booked specifically to attend the intervention as well as potential cancelations of clinics in the control group. Participants will be informed about their allocation at the time of receiving instructions with the QMUL VLE platform access. At this time, the control group will be informed about timings of gaining their access to the full intervention and all resources provided to the experimental group after final assessments are completed. Participants will be informed that they are free to withdraw at any time without needing to provide a reason and with no penalties or detrimental effects.

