### Study aims and objectives

The primary aim of this study is to determine the feasibility of an educational intervention to advance clinicians’ application of instrumented gait analysis in children and young people with cerebral palsy, to inform the design of a full trial. Objectives are as follows:

To establish the feasibility of a future randomised controlled trial of educational intervention.Assess the rate of participant enrolment, retention and compliance with intervention.Assess whether the inclusion and exclusion criteria for participants are appropriate.Assess whether the duration of intervention is appropriate.Assess whether intervention delivery in a virtual learning environment is feasible and acceptable.Explore if the outcome measures are appropriate for the study aims.Define the sample size for a definitive trial.Explore the fidelity of intervention delivery.Further understand the barriers and facilitators of the intervention.

The secondary aim is to measure the effect that appropriate IGA training and its delivery has on physiotherapists’ knowledge, skills and attitudes.

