### Trial design

This will be a two-arm feasibility randomised controlled trial with an experimental and control group. The 6-week on-line intervention delivered as part of the trial is a stand-alone, post-graduate level educational course called Virtual Gait Analysis Course for Paediatric Physiotherapists (VGAPP). Eligible physiotherapists who consent to take part in the study will be randomly allocated into experimental and control groups. A repeated measures design will be adopted, whereby participants will complete outcome measures at baseline, immediately after the intervention, and at 4 months. This will include collection of feedback as part of a full process evaluation.

The trial will be determined feasible if a priori set criteria based on primary outcome measures and included in the process evaluation will be achieved at or above agreed levels (see the ‘Outcome measures’ section of ‘Methods’). After conducting and reviewing outcomes of the full evaluation process, the decision about delivery of the definitive trial will be made.

Figure 1 shows the study flow diagram, and Table 1 indicates the schedule of enrolment, intervention, and outcome measures [18].

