### Data collection, management, and analysis

In line with accepted practice for feasibility studies, no power analysis will be conducted, and all analyses will be exploratory only [29]. Data analysis will be performed after the last trial participant has completed final assessments (outcomes at 4 months post intervention). Data will be managed initially in Microsoft Excel software and analysed using IBM SPSS statistics software. Table 3 provides a summary of outcome measures, hypotheses, and analysis planned in the study.

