#### Data management and research governance

A baseline table (descriptive statistics and frequencies) will compare the demographic and clinical characteristics including gender, age, experience, education, practice setting, contract type, study leave availability to participate in intervention, access to equipment, and gait analysis training. The primary outcomes will be reported using descriptive statistics. The quantitative variables will be presented as means and standard deviations.

A preliminary analysis of between-group differences will be conducted to determine the range of potential effect sizes from repeated measures ANOVA. Feasibility outcomes will be presented as number of participants meeting the a priori definitions. Kendall’s tau-b (*τ*_b_) correlation coefficient will be used to measure of the strength and direction of association that exists between two variables measured on at least an ordinal scale. To explore the extent and patterns of missing outcome data, we will report the proportion of missing values per item and the proportion of participants who will complete all items on the questionnaires. The proportion of missing data will also be reported for the other key outcomes and compared between the participants from intervention and control groups.

Qualitative data will be analysed according to the framework approach [30], a realist approach located within an interpretivist frame. The opinions and experiences of participants will be explored to understand any barriers and facilitators related to running of the educational intervention. During active familiarisation, the textual data will be coded, and codes will be organised into themes and subthemes to construct a thematic framework to aid indexing. To ensure rigour and consistency, the analysis process will undergo investigator triangulation. In this process, different observers, examiners, and analysts will compare and check data collection and/or interpretation [30, 31]. Qualitative data will be presented as quotes and descriptive summaries.

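### Colleagues from one trust are randomised together, but the between-group analyses of the secondary outcomes treat participants as individually randomised, so those confidence intervals can be too narrow

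*Protocol article*

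**What the plan says.** Two descriptions of allocation stand in the protocol article. Under Trial design: "Eligible physiotherapists who consent to take part in the study will be randomly allocated into experimental and control groups". Under Allocation, concealment mechanism, and implementation: "Participants will be assigned to groups randomly", followed in the same paragraph by "To avoid contamination, participants from the same healthcare trusts will be randomised to the same group".

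The Sample size section states that "the target sample size will be of a minimum 12 participants per trial arm; therefore, a minimum of 24 in total is anticipated". The section Data collection, management, and analysis adds that "no power analysis will be conducted, and all analyses will be exploratory only".

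For the secondary outcomes, Table 3 gives effect sizes and 95% CIs from repeated measures ANOVA (knowledge, skills, attitudes), with Kruskal–Wallis as well for knowledge and skills. The Abstract names a two-way mixed ANOVA. Data management and research governance says: "A preliminary analysis of between-group differences will be conducted to determine the range of potential effect sizes from repeated measures ANOVA". None of these places mentions trust, employer or clustering.

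The objectives include "Define the sample size for a definitive trial". Process evaluation and implementation outcomes returns to that sample size. Neither place mentions an ICC, a cluster size or a design effect.

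**The concern.** A rule that keeps colleagues together makes the trust the randomised unit for anyone who shares one; a participant alone in a trust is a cluster of one. The stated reason is contamination, so the authors allow for colleagues enrolling together, and the Recruitment section includes emails to team leads. Colleagues may share caseload, equipment and study-leave arrangements, so their scores may be correlated.

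The within-person factor in the ANOVA handles the repeated timepoints. It does nothing for correlation between colleagues, and Kruskal–Wallis also assumes independent participants. If that correlation is positive and trusts are shared, the standard error of a between-group difference is understated. The resulting range of effect sizes is meant to inform the definitive trial, so an interval that is too narrow gives that trial's planners false precision. A definitive sample size worked out as if individuals were randomised could then also be too small.

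**Working it through.** **The plan's own figure.** 2 arms × 12 = 24. It reproduces, but it has no power or precision basis; the protocol gives no effect size, SD, alpha or power. No definitive sample size is stated, so none can be checked.

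**Inputs.** From the protocol: 12 per arm, 95% CIs, same-trust allocation. Assumed, because the protocol gives neither: m participants per trust (1 to 4, equal sizes) and ICC 0.05 to 0.20.

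**Formulas.** Design effect DE = 1 + (m − 1) × ICC. CI width is multiplied by √DE. Effective sample size = 24/DE. The unadjusted half-width of a 95% CI for a difference at one timepoint is t(0.975, 22 df) × √(2/12) = 2.074 × 0.408 = 0.847 SD. Coverage is by simulation: 40,000 runs, 12 per arm, one timepoint, interval ignoring trust.

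| m | DE | Half-width allowing for trust (SD) | Effective N of 24 | Coverage of unadjusted 95% CI |
|---|---|---|---|---|
| 1 | 1.00 | 0.847 | 24.0 | 95% |
| 2 | 1.05–1.20 | 0.868–0.928 | 22.9–20.0 | 94.5%–92.7% |
| 3 | 1.10–1.40 | 0.888–1.002 | 21.8–17.1 | 94.1%–90.0% |
| 4 | 1.15–1.60 | 0.908–1.071 | 20.9–15.0 | 93.3%–87.5% |

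Each range runs from ICC 0.05 to ICC 0.20. The half-widths do not yet include the loss of degrees of freedom from having few clusters.

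**Mostly single participants.** With 16 participants alone in their trust and 4 pairs (two pairs per arm), the average DE is 1 + (4/12) × ICC, or 1.03 at ICC 0.1 and 1.07 at ICC 0.2. Simulated type I error is about 5.4% and 5.9% against a nominal 5%.

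**Change from baseline.** Write a score as group mean + trust effect + person effect + occasion error. If the trust effect is the same at both occasions, it drops out of the difference. Simulation agrees: with 6 trusts of 4, ICC 0.2 and an assumed within-person correlation of 0.6, type I error is 5.0%. A trust effect that changes over time, such as a shared opportunity to apply the learning, does not drop out and could inflate the error more.

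**Definitive trial, for illustration only.** Assume a standardised difference of 0.5, two-sided 5% and 80% power: 63 per arm, 126 in total, if individuals are independent. Multiplying 63 by DE and rounding up gives totals of 134–152 (m = 2), 140–178 (m = 3) and 146–202 (m = 4). Left at 126, power falls to 78%–73%, 76%–66% and 74%–60%. As a share of the required number, the shortfall at m = 4 is 1 − 1/1.15 = 13% to 1 − 1/1.60 = 37.5%.

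**The case against.** The strongest reply is that the trial's decisions do not rest on these intervals. Recruitment, retention and engagement are descriptive and progression is judged on them; satisfaction is descriptive and the interviews are analysed qualitatively. The secondary comparisons are labelled exploratory. This stands, and it limits the weight of the point. A reader might infer from the allocation rule that every planned analysis is faulty; the document does not support that.

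Second, the document does not show that trusts will be shared. Recruitment is UK-wide through a national network, bulletins and social media as well as team leads, and private practice is eligible. This also stands: the effect may be small or nil.

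Third, the coverage figures describe a single timepoint, whereas the plan is a repeated measures model with a baseline. A stable trust effect cancels from the group-by-time contrast. That stands for stable effects and fails for effects that change over time, so the table does not give the error of the planned model.

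Fourth, a reader might infer that the definitive sample size will be too small. The document states neither that number nor a formula. Ignoring trust does not shift the expected mean difference. A shortfall needs the later trial to keep the rule and to omit a design effect, so it is a risk and not a stated error.

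Fifth, handling of trust could sit in an analysis plan that is not shown. That does not remove the point: the article names its methods, and those methods do not match its own allocation rule. Nor does the exploratory label make a 95% CI valid.

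**Conclusion.** The point holds for the between-group comparisons of knowledge, skills and attitudes. The allocation rule makes the trust the unit wherever it is shared, and the named analyses do not reflect that. The CIs can be too narrow if at least some trusts supply two or more participants and scores within a trust are positively correlated.

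Under the assumed 2 to 4 per trust and ICC 0.05 to 0.20, single-timepoint coverage lies between about 94.5% and 87.5%. The lower end needs all 24 participants in trusts of four. With mostly single participants the loss is under one percentage point; with no shared trusts it is nil; for change from baseline with a stable trust effect it is close to nil.

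The primary feasibility outcomes and the progression criteria are not affected. This should be fixed, but it does not threaten the trial's main purpose.

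**What to change.** - In the allocation section, state that the trust (or employing organisation, for private settings) is the unit of randomisation, and bring the Trial design wording into line.
- Report the number of trusts and the number of participants per trust, by arm.
- For the secondary between-group comparisons, account for trust, at least as a sensitivity analysis: a random trust effect with a small-sample correction, or cluster-level or small-sample cluster-robust inference. With mostly single participants or pairs a random trust effect will be poorly estimated, which is a reason to name an alternative in advance.
- If the definitive trial keeps the same-trust rule, multiply its sample size by 1 + (m − 1) × ICC over a range of assumed ICCs. Twenty-four participants cannot estimate an ICC usefully, so the range should not rest on this trial's estimate.

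Cost: some wording, an organisation code that the allocator needs anyway, and no extra participants. The CIs become wider, possibly much wider if there are few large trusts. With 6 trusts of 4 and ICC 0.2, the degrees of freedom fall from 22 to 6 − 2 = 4, and the width is multiplied by √1.60 × 2.776/2.074 = 1.69, so about 69% wider.

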### Data collection, management, and analysis

In line with accepted practice for feasibility studies, no power analysis will be conducted, and all analyses will be exploratory only [29]. Data analysis will be performed after the last trial participant has completed final assessments (outcomes at 4 months post intervention). Data will be managed initially in Microsoft Excel software and analysed using IBM SPSS statistics software. Table 3 provides a summary of outcome measures, hypotheses, and analysis planned in the study.

#### Data management and research governance

A baseline table (descriptive statistics and frequencies) will compare the demographic and clinical characteristics including gender, age, experience, education, practice setting, contract type, study leave availability to participate in intervention, access to equipment, and gait analysis training. The primary outcomes will be reported using descriptive statistics. The quantitative variables will be presented as means and standard deviations.

A preliminary analysis of between-group differences will be conducted to determine the range of potential effect sizes from repeated measures ANOVA. Feasibility outcomes will be presented as number of participants meeting the a priori definitions. Kendall’s tau-b (*τ*_b_) correlation coefficient will be used to measure of the strength and direction of association that exists between two variables measured on at least an ordinal scale. To explore the extent and patterns of missing outcome data, we will report the proportion of missing values per item and the proportion of participants who will complete all items on the questionnaires. The proportion of missing data will also be reported for the other key outcomes and compared between the participants from intervention and control groups.

Qualitative data will be analysed according to the framework approach [30], a realist approach located within an interpretivist frame. The opinions and experiences of participants will be explored to understand any barriers and facilitators related to running of the educational intervention. During active familiarisation, the textual data will be coded, and codes will be organised into themes and subthemes to construct a thematic framework to aid indexing. To ensure rigour and consistency, the analysis process will undergo investigator triangulation. In this process, different observers, examiners, and analysts will compare and check data collection and/or interpretation [30, 31]. Qualitative data will be presented as quotes and descriptive summaries.

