***Primary***			
Recruitment	Study will recruit 24 participants	Number of participants	Descriptive statistics
Retention	Study will retain 75% of sample	Number of participants	Descriptive statistics
Engagement	The average proportion of completed VLE items will be ≥ 66%	Average proportion of completed VLE items	Descriptive statistics

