***Secondary***			
Knowledge	EG will have improved knowledge scores relative to CG EG will increase knowledge scores EG will maintain knowledge scores	MCQ test	Effect sizes and 95% CIs from repeated measures ANOVA test and Kruskal–Wallis *H*-test
Skills	EG will have improved practical skills scores relative to CG EG will increase practical skills scores EG will maintain practical skills scores	OSCE	Effect sizes and 95% CIs from repeated measures ANOVA test and Kruskal–Wallis *H*-test
Attitudes	EG will have improved gait-related practice behaviours	Questionnaires: Self-reported knowledge and confidence, practice change, practice change planning, beliefs, semi-structured interviews	Effect sizes and 95% CIs from repeated measures ANOVA test Framework method for qualitative data (Ritchie 2014)
Satisfaction	EG will demonstrate a high satisfaction rate	Satisfaction questionnaire	Descriptive statistics

*EG* experimental group, *CG* control group, *VLE* virtual learning environment, *MCQ* multiple-choice question, *OSCE* observed standardised clinical examination

Recruitment will be determined as feasible if study is able to recruit 24 participants within 4 months [22, 23]. Retention rates will be considered at two stages: (1) from expression of interest to consent — it will be deemed feasible if greater than 50%, and (2) from consent to course completion — it will be deemed feasible if greater than 75% [24, 25]. Additionally, engagement (participants’ interactions with an online system) data will be collected during intervention via the analytics tools in the QMUL Virtual Learning Environment which log the detail of activity access, time, and completion for each component. These analytic tools are part of the general-purpose dashboard and provide an algorithmic representation of student online behaviours based on whether the behaviour occurred and for how long, rather than quality of these behaviours. Previous studies show that these analytics have been positively correlated with student performance [26–28]. It will be deemed feasible if the average proportion of completed learning sessions and tasks will be ≥ 66%.

Secondary outcomes are as follows: knowledge, skills, attitudes, and satisfaction will be collected via online questionnaires (SurveyMonkey) and during skill tests (OSCE). Knowledge, skills, and attitudes will be collected at three timepoints (Table 1).

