Baseline comparisons will be conducted to detect any substantial differences between participants recruited from the control and intervention arms. Sample size and anticipated effect size defined for the definitive trial will be reviewed and assessed for feasibility. Participant withdrawals and number of participants lost to follow-up (and where possible reasons and participants’ key baseline characteristics) will be analysed. The study protocol adherence will be reviewed within the research team. Fidelity to the trial protocol including follow-up, dosage of the intervention, crossover between study arms, and adherence to intervention delivery plan will be assessed against study protocol and participant timelines. Any changes to the protocol will be reported.

Furthermore, appropriateness of the trial design for the trial aim, inclusion and exclusion criteria, outcome measures, and intervention components will undergo an exploratory analysis of participants’ outcomes, engagement with content, and assessments, together with qualitative analysis of participants and educators’ feedback. Sustained participant interest throughout the trial period and sustained staffing levels to deliver and facilitate participants’ learning journey during intervention will be explored to inform the sustainability criteria for the definitive trial. The implementation cost analysis will be explored with the aim to inform the design of a full cost-utility analysis alongside a future definitive trial. Implementation cost will include the cost of administration involved in running the trial and cost related to production and delivery of the intervention and assessment components — such as speaker fees, and OSCE examiners and moderators will be reviewed.

In addition, the COM-B model and the behaviour change techniques taxonomy (BCTT) [35], widely used frameworks in behaviour change and implementation research, will support the process evaluation analysis and an in-depth exploration of the barriers and facilitators of implementing the feasibility trial.

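### The only target effect the protocol offers for sizing the definitive trial is the one observed in about 18 to 24 participants, which is too imprecise to fix a sample size

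*Protocol article*

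**What the plan says.** *Study aims and objectives* lists, among the feasibility objectives, "Define the sample size for a definitive trial". The input that bears on it is in *Data management and research governance*: "A preliminary analysis of between-group differences will be conducted to determine the range of potential effect sizes from repeated measures ANOVA". Table 3 gives the corresponding output for knowledge, skills and attitudes as "Effect sizes and 95% CIs from repeated measures ANOVA test". *Process evaluation and implementation outcomes* then refers back to the result: "Sample size and anticipated effect size defined for the definitive trial will be reviewed and assessed for feasibility".

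On size, *Sample size* states that "the target sample size will be of a minimum 12 participants per trial arm", and Table 3 sets the retention target as "Study will retain 75% of sample". *Data collection, management, and analysis* adds that "no power analysis will be conducted, and all analyses will be exploratory only". The article also plans means and standard deviations for quantitative variables, and reports of retention, withdrawals and missing data.

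**The concern.** Three statements line up: an objective to set the definitive-trial sample size, an analysis to find potential effect sizes, and a later review of a sample size and anticipated effect size already defined. Nothing else in the article could supply the target effect. It mentions no important difference on the MCQ test or the OSCE and no effect from another study.

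Sample size varies with the inverse square of the effect, so an imprecise effect gives a far more imprecise sample size. If the target is taken from a chance-high estimate, the definitive trial is underpowered. If it is taken from a chance-low estimate, the trial is larger than it needs to be. If the estimate is zero or negative, there is no sample size at all. The choice of 24 for the feasibility trial is not at fault. The issue is what its effect estimates are used for.

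**Working it through.** **Inputs from the article.** 12 per arm, 24 in total (*Sample size*). Retention target 75% (Table 3): 24 × 0.75 = 18, about 9 per arm. The article has no power-based figure to reproduce.

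**Assumptions, not in the article.** Two-sided 5%, 80% power, SD = 1, equal arms, true standardised difference d between 0.3 and 1.0, baseline correlation 0 to 0.7.

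**1. Precision of the observed effect.** With n per arm, t = d√(n/2) on 2n − 2 df, and the exact 95% CI comes from the noncentral t distribution. For d = 0.5, t = 0.5 × √6 = 1.22 (12 per arm) or 0.5 × √4.5 = 1.06 (9 per arm).

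| Observed d | 95% CI, 12 per arm | 95% CI, 9 per arm |
|---|---|---|
| 0.5 | -0.32 to 1.31 | -0.45 to 1.43 |
| 0.8 | -0.04 to 1.63 | -0.18 to 1.75 |

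**2. What that range implies for the next trial.** n per arm = 2 × ((1.96 + 0.8416)/d)² = 15.7/d². At d = 0.5 this is 63 (64 by the exact t calculation). At the upper limits it is 15.7/1.31² → 10 and 15.7/1.43² → 8. At the lower limits no n exists. The range therefore runs from a handful per arm to no computable number.

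**3. Consequence of sizing on the observed effect.** Feasibility trials with 12 per arm were simulated. The next trial was sized on each positive observed d (no small-sample correction), and its real power was found from the noncentral t distribution.

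| True d | Needed per arm | Real power below 50% (positive estimates) | Estimate has wrong sign (all trials) |
|---|---|---|---|
| 0.5 | 64 | 35% | 11% |
| 0.8 | 26 | 27% | 2.5% |
| 1.0 | 17 | 20% | 0.7% |

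At true d = 0.5 the middle half of the calculated sizes runs from about 23 to 150 per arm. With the small-sample correction to d, and power from the normal approximation, the three power percentages are 32%, 21% and 13%.

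**4. Sensitivity to true effect and baseline adjustment.** Chance that n is more than two-fold off or cannot be computed (bias-corrected d; baseline adjustment represented as d/√(1 − ρ²)), shown as 12 / 9 per arm:

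| True d | Unadjusted | ρ = 0.7 |
|---|---|---|
| 0.3 | 79% / 82% | 71% / 75% |
| 0.5 | 66% / 70% | 55% / 60% |
| 0.8 | 50% / 55% | 35% / 42% |
| 1.0 | 38% / 44% | 26% / 33% |

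**5. If the ANOVA effect size is partial eta-squared.** Under no effect its expected value is df1/(df1 + df2). For group × time with three time points and two arms this is 2/(2 + 44) = 0.043 with 24 complete cases and 2/(2 + 32) = 0.059 with 18. In Cohen's f these are 0.21 and 0.25, so an apparent effect is expected where none exists.

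**6. The alternative.** Fix the important difference in outcome units and take only the SD from this trial. The upper one-sided 80% limit for the SD is √(df/χ²₀.₂₀) times the observed SD: 1.16 at 22 df and 1.20 at 16 df. Using the observed SD itself, n falls within half to double the correct value in 97% (12 per arm) or 94% (9 per arm) of trials. Real power is below 60% in 9% or 13% of trials, and in 1.5% or 2.6% if the upper limit is used. Sizing on a positive observed d at true d = 0.5 gives below 60% in 41% or 44%.

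**The case against.** The strongest reply is that a reader might infer that the protocol says the definitive sample size will be computed from the observed effect, and it does not. It speaks of a preliminary analysis and a range, plans confidence intervals, and calls all analyses exploratory. How the anticipated effect size is to be defined is left unsaid, and a fuller document may say. This stands as a limit on the wording: the link is inferred from several sections. It does not remove the point, because the observed range is the only source of a target effect that the article names, and section after section points to it. Reporting the range with its interval does not help, since the range does not determine a number.

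Four further limits stand.

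- The SD and retention are already planned outputs, so the gap is in how they are used for sizing.
- A reader might infer that a low estimate would stop the definitive trial. *Trial design* ties feasibility to criteria on the primary outcomes, which in Table 3 are recruitment, retention and engagement. There is no effect-size threshold.
- The article names no effect-size metric, so the partial eta-squared figures are conditional.
- 24 is a minimum, and the text under *Outcome measures* asks for more than 75% retention, measured to course completion. Eighteen is therefore the count at the threshold and not a forecast of who will be analysed at 4 months.

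**Conclusion.** The point holds in a limited form. The article sets out to define the definitive-trial sample size and offers only the effect observed in this trial as a target. At 12 per arm, or about 9 at the retention threshold, that effect is known to roughly ±0.8 or ±0.9 SD. This is too wide to fix a sample size, whichever end of the range is used.

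The interval widths rest only on the planned numbers and a two-arm comparison of means. The power consequences rest on assumed true effects and apply only if the observed effect is used for sizing. A reader might infer that the definitive trial is likely to be badly mis-sized in any event. That is supported for small to moderate true effects. At a true d of 1.0, or 0.8 with a baseline correlation of 0.7, the chance of a more than two-fold error is 26% to 44%, which is below one half but still material. Keeping participants from one trust in the same group would reduce the information somewhat further, by an amount the article does not allow one to calculate.

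**What to change.** In *Data management and research governance* and in *Process evaluation and implementation outcomes*, state that the definitive trial will be sized on a minimum important difference in its chosen primary outcome (MCQ test or OSCE), set with the stakeholder group independently of the effect observed here.

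State what this trial will contribute to the calculation:

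- the SD already planned, with its upper one-sided 80% limit (1.16 times the observed SD at 22 df, 1.20 times at 16 df);
- retention;
- the baseline-to-follow-up correlation;
- same-trust cluster sizes.

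Report observed group differences with confidence intervals as descriptive only.

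The cost is a few sentences and one question to a stakeholder group that already exists. The definitive-trial number may be larger: using the upper SD limit alone multiplies it by 1.16² = 1.35 at 22 df or about 1.43 at 16 df.
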